#### Final visit

The final visit will take place between months 18 and 24 (depending on enrolment date to avoid the possibility that the final visit takes place during university summer break) and will include an extensive clinical examination by a gynaecologist for signs suggestive of PID and, if indicated, pelvic ultrasound. The gynaecologist will have access to chlamydia test results for both groups. For participants in the control group, the gynaecologist will review Ct results throughout the course of the study and decide whether the participant should get treatment based on these results. Final visits will take place at the hospital gynaecology department in geographical proximity to the recruiting universities: Poissy/Saint-Germain-en-Laye Hospital, Nice L’Archet Hospital, Paris Cochin Hospital and Bordeaux Pellegrin Hospital.

In the case where participants do not complete follow-up, attempts will be made to obtain information on the reasons for dropout. The last contact date will be recorded. To compensate participants for the time dedicated to the study, financial compensation will be given at the initial visit and at the final visit.

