## Methods/design

### Design/setting

This is a randomised controlled trial spanning 24 months. It is a single-blinded study nested within the i-Share cohort study (Fig. 1).

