#### Control group

The control group will perform self-taken vaginal samples at the same frequency as the intervention group, but testing will be deferred until the end of the 18-month study period to allow study of the natural course of Ct infection in the absence of testing and treatment. Results for Ct will be made available to the gynaecologist at the final visit for adequate care. During the whole study, participants will follow current screening guidelines (i.e., screening in case of symptoms or if they attend STI clinics).

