### Blinding

Participants will be blinded to their group assignment until the end of the trial except for those who will be informed of a positive result in the intervention group. Two independent experts will review symptoms data from medical records and symptoms collected during the final visit to classify outcome status (confirmed, probable or no PID). These medical experts will be blinded to group assignments and Ct status.

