#### Randomisation

Block randomisation, stratified by participating university (Versailles Saint-Quentin-en-Yvelines, Bordeaux, Nice Sofia-Antipolis, Paris Sorbonne Universités, and Sorbonne Paris Cité), will be used to assign eligible participants who have provided informed consent to each group (1:1 ratio), resulting in one intervention group and one control group. Site-specific randomisation will be performed in the UHS of each of the five participating universities by the principal investigator at each site on the Cleanweb® electronic platform as soon as student recruitment is registered during the initial visit. Group assignment is generated at the same time as the participant’s study identification number; only principal investigators at each site and dedicated staff from the Centre National de Référence (French National Reference Centre for Chlamydial Infections) (CNR) have access to group assignment.

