### Outcomes

#### Primary endpoint

The primary endpoint measure is the cumulative incidence of first PID over 24 months in the intervention group (immediate testing and treatment) and in the control group following current screening recommendations (deferred testing). PID comprises a spectrum of inflammatory disorders of the female upper genital tract, including endometritis (inflammation of the uterine lining), salpingitis (inflammation of one or both fallopian tubes), tubo-ovarian abscess and pelvic peritonitis.

For the purpose of this study, the definition of PID is as follows [20]:
*Probable PID:* Clinical diagnosis of PID (pelvic pain, cervical motion tenderness, uterine or adnexal tenderness)
*Confirmed PID:* Clinical diagnosis of PID and one of the following criteria: laparoscopic abnormalities consistent with PID, endometrial biopsy with histopathologic evidence of endometritis, pelvic ultrasound showing thickened tubal wall (>8 mm), tubal fringes or free pelvic fluid

Data on symptoms reported by the participants and collected through medical records, as well as data collected at the final visit, will be reviewed by two independent experts blinded to group allocation (intervention or control) and to Ct infection status to classify the outcome status (no PID, probable PID or confirmed PID).

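### The gynaecologist collecting PID findings at the final visit can see Ct results and in effect the arm; the order of recording and release should be fixed

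*Protocol article*

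**What the plan says.** The Final visit section states that the visit "will include an extensive clinical examination by a gynaecologist for signs suggestive of PID and, if indicated, pelvic ultrasound". It continues: "The gynaecologist will have access to chlamydia test results for both groups", and "For participants in the control group, the gynaecologist will review Ct results throughout the course of the study" before deciding on treatment. The Control group section gives the purpose: "Results for Ct will be made available to the gynaecologist at the final visit for adequate care".

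These findings reach the primary endpoint. The Primary endpoint section sends symptom data from participants and from clinical files to the experts and then adds: "as well as data collected at the final visit, will be reviewed by two independent experts blinded to group allocation (intervention or control"). The same sentence says that Ct infection status is hidden from them too. The Blinding section repeats this for the experts: "These medical experts will be blinded to group assignments and Ct status". Besides the experts, it lists only the participants as blinded, apart from intervention women told of a positive result. Design/setting describes the trial in these terms: "It is a single-blinded study nested within the i-Share cohort study".

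The Randomisation section restricts knowledge of the arm: "only principal investigators at each site and dedicated staff from the Centre National de Référence" have access to group assignment. Final-visit gynaecologists are not named there.

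**The concern.** Probable PID is a clinical diagnosis from pain and from tenderness on examination, and the Statistical analyses section counts probable and confirmed PID together first. Tenderness is a matter of judgement, and ultrasound at this visit is discretionary. An examiner who knows that a woman has a positive swab on which the study did not act may look harder, record an equivocal sign or order a scan more readily. Expert blinding protects the classification step. It cannot undo a difference in what was elicited, recorded or imaged.

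The access also undercuts the Randomisation section. A clinician whose task differs by arm learns the arm without being on the list of those who may know it.

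The final visit is planned for all participants and few PID cases are expected, so a handful of additional records in one arm could move the primary relative risk.

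**Working it through.** **Reading the sections together**

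1. The same person examines, decides on ultrasound and has the Ct results (Final visit).
2. For controls only, that person reviews deferred results and decides on treatment, so the arm can be inferred (Final visit, Control group).
3. The recorded findings go to the experts (Primary endpoint), who are blinded but see only that record.
4. No section says whether results are opened before or after the examination. An informed examination is therefore permitted, but not stated to occur.
5. The confirmed-PID analysis is only a partial safeguard. It still needs the clinical diagnosis, and the final-visit ultrasound depends on the same examiner.

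**How large could it be?** The article gives no figure for examiner influence, so this is an illustration.

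Inputs from the Sample size section:
- 2000 per arm and 10% attrition: 2000 × 0.9 = 1800 evaluable.
- One-sided 5% test.
- Baseline Ct prevalence 5% and incidence 5% per year. Over 18 months, 5% + 95% × 5% × 1.5 ≈ 12% of controls have a positive swab, about 216 of 1800.

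Assumptions not in the article:
- PID risks of 2.77% (control, about 50 cases) and 1.55% (intervention), ratio 0.56. The article gives no arm-level risks. Solving for the control risk that gives 80% power at RR 0.54 with 1800 per arm yields 2.45%; building it from the 5%/12% scenario yields 3.07%. The value 2.77% lies between them.
- f = proportion of women with a known positive result who gain a PID record because of it: 2%, 5% or 10%.
- q = proportion of intervention women exposed to the same influence: 0, 5% or 12%.

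Under no true effect, the observed risks are a = 0.0277 + 0.12f (control) and b = 0.0277 + qf (intervention). With p the mean of a and b, the rejection probability is

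Φ{ [(a − b) − 1.645 √(2p(1 − p)/n)] / √([a(1 − a) + b(1 − b)]/n) }.

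Example, f = 5% and q = 0: a = 0.0337, b = 0.0277, a − b = 0.0060. Both standard errors are about 0.00575, so (0.0060 − 0.00946)/0.00575 = −0.60 and Φ = 0.27.

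For the apparent RR when the true RR is 0.56, the intervention risk is 0.0155 + qf.

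| q | Extra control cases (f = 2/5/10%) | Extra intervention cases | Null rejection | Apparent RR, true RR 0.56 |
|---|---|---|---|---|
| 0 | 4/11/22 | 0/0/0 | 11/27/64% | 0.52/0.46/0.39 |
| 5% | 4/11/22 | 2/4.5/9 | 8/15/30% | 0.55/0.53/0.52 |
| 12% | 4/11/22 | 4/11/22 | 5/5/5% | 0.60/0.64/0.69 |

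The result depends on q as much as on f. With equal exposure the test keeps its 5% level under the null, and a true benefit is diluted.

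**The case against.** **Order is not stated.** The article grants access for the purpose of care, and the treatment decision for controls can follow the examination. The sequence of steps within a visit is often left to the full protocol. This stands in part: the article cannot be read as saying that results are always seen first. But it states the access outright and rests its protection of the outcome on the experts alone.

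**Not all endpoint data are involved.** A reader might infer that the primary endpoint as a whole is collected unblinded to study swab results. The documents do not support that. PID is also captured at emergency department, general practitioner and gynaecologist visits during follow-up, when control swabs are still untested. The share of cases first found at the final visit is not given.

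**Direction is not certain.** A reader might also infer that a bias in favour of screening is established. It is plausible, because the study did not act on control positives. But intervention women also have positive results on file, and during follow-up they are sent to a physician who knows the result and returns clinical findings. That separate route could add PID records in the intervention arm. The 12% also ignores testing and treatment that controls may obtain under current guidelines.

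**Safeguards exist.** Most participants do not know their arm, pain is also self-reported during follow-up, and a confirmed-PID analysis is planned. These reduce the problem without removing it.

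**Conclusion.** The weakness is real and confined to final-visit data: the text allows the examiner to know Ct status, and in effect the arm, while collecting findings that define the primary endpoint, and blinded classification cannot correct that. The Final visit and Randomisation sections also need to be reconciled on who may learn the arm.

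A bias towards screening is the likelier direction, but neither direction nor size is established. Across the assumptions shown, null rejection runs from the nominal 5% to 64%; the upper end requires a strong examiner effect and no exposure in the intervention arm. This is a should-fix point: the size is unknown, but the route into the primary endpoint is direct and inexpensive to close.

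**What to change.** Within the same final visit:

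1. The gynaecologist records the examination findings, the ultrasound indication and, if a scan is done, its result. This record is locked before Ct results and arm are released to that clinician.
2. The results are then released, and care proceeds as the protocol already provides. Any imaging or care decided after release is left as it is.
3. For final-visit data, the experts classify the primary endpoint on the locked findings. Anything found after release is recorded and flagged separately for a sensitivity analysis.
4. The Blinding, Randomisation and Final visit sections state this order and say when the final-visit gynaecologist may learn the arm.

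The cost is one extra recording step, with results opened slightly later in the visit. No added visit, staff or procedure is needed, and the sample size does not change. Blinding stays incomplete where an informed intervention participant mentions her result. Enrolment began in January 2017 and final visits start at month 18, so none was due before July 2018; when the article appeared in November 2017 the step could still have covered every final visit.

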### Outcomes

#### Primary endpoint

The primary endpoint measure is the cumulative incidence of first PID over 24 months in the intervention group (immediate testing and treatment) and in the control group following current screening recommendations (deferred testing). PID comprises a spectrum of inflammatory disorders of the female upper genital tract, including endometritis (inflammation of the uterine lining), salpingitis (inflammation of one or both fallopian tubes), tubo-ovarian abscess and pelvic peritonitis.

For the purpose of this study, the definition of PID is as follows [20]:
*Probable PID:* Clinical diagnosis of PID (pelvic pain, cervical motion tenderness, uterine or adnexal tenderness)
*Confirmed PID:* Clinical diagnosis of PID and one of the following criteria: laparoscopic abnormalities consistent with PID, endometrial biopsy with histopathologic evidence of endometritis, pelvic ultrasound showing thickened tubal wall (>8 mm), tubal fringes or free pelvic fluid

Data on symptoms reported by the participants and collected through medical records, as well as data collected at the final visit, will be reviewed by two independent experts blinded to group allocation (intervention or control) and to Ct infection status to classify the outcome status (no PID, probable PID or confirmed PID).

#### Secondary endpoints

The following secondary endpoints will be measured:Prevalence of Ct infection in participants at baseline (intervention and control groups)Incidence of first Ct infection in participants with a negative Ct test result at baseline (intervention and control groups)Incidence of first PID (intervention and control groups)Duration of Ct infection (6 or 12 months or over 18 months because the time window between each assessment is 6 months); proportion of infections associated with a diagnosis of PID (whether at a previous visit or concurrently) and time to development of PID since Ct infection; proportion of spontaneous Ct infection resolution (control group), defined as a Ct-negative sample after one or more Ct-positive samplesIncidence of reinfections (intervention and control groups); an algorithm to differentiate between Ct reinfection, treatment failure and persistent infection [21] will be developed on the basis of typing (as described below in laboratory analyses), treatment, partner notification and change of partner

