#### Follow-up

All participants will self-collect vaginal samples in the privacy of their home at months 6, 12 and 18. A kit including detailed self-sampling instructions will be mailed to them a few days prior to each due date. Participants will mail the sample back to the CNR and complete an electronic self-administered questionnaire about their number of sexual partners, condom use, symptoms such as abnormal vaginal discharge or pelvic pain, additional testing since their previous sample, medical visits and antibiotic use (for Ct or other infections).

Participants with a positive test result for Ct at baseline or months 6, 12 or 18 in the intervention group will be referred to their physician or the nearest STI clinic for treatment. Of note, current recommendations for uncomplicated infections include a single-dose therapy of azithromycin (1 g) or a 7-day course of doxycycline [18].

The physician collecting clinical data upon examination will fill out a specific form, handed out by the participant together with a prepaid envelope, on clinical findings, as well as treatment initiated, results of additional tests or ultrasound (if any), and information regarding whether a partner was treated (if available). These data will be received at the UHS and entered by a trained clinical research assistant on the Cleanweb® platform.

At any moment during follow-up, all participants will be asked to complete a short, self-administered questionnaire online each time they feel unusual lower abdominal pain. A contact will be made with the participant 24–48 h after completion of this short pelvic pain questionnaire to encourage the participant to visit the closest participating gynaecology emergency department (GED), where they will be evaluated for PID according to current national recommendations by the Collège National des Gynécologues et Obstétriciens Français [19]. Data from these visits to the GED will be made available to the trained clinical research assistant, who will collect them using a standardised clinical research form and enter the clinical data on the Cleanweb® platform.

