### Statistical analyses

For the primary analysis, we will calculate the cumulative incidences of developing PID over 24 months in both groups and estimate the RR of developing PID as the ratio of these incidences (intention-to-treat analysis). We will consider probable and confirmed PID together first and conduct confirmatory analysis restricted to confirmed PID only.

For comparison with previous trials, we will further stratify our RR analysis on baseline status of Ct infection. We will also conduct an exploratory Cox regression analysis to adjust the RR of developing PID for other baseline characteristics of the participants. Missing data imputation will be considered for participants’ characteristics (excluding Ct and PID status) when missing values exceed 10%.

As secondary analyses, we will determine the following:Annual incidence of Ct infection based on the first recorded Ct infection among participants Ct-negative at baseline in both groupsAmong participants in the control group with incident Ct infection (participants Ct-negative at baseline), proportions (and 95% CIs) of Ct infections with spontaneous resolution and of Ct infections evolving towards PID; estimation of the duration of Ct infection (from Ct detection to clearance) and time to develop PID (time between incident Ct infection and incident PID, defined as from 3 months before Ct detection because time windows correspond to 6 months, to the onset of PID symptoms)Among participants in both groups who have cleared Ct infection at least once, incidence of Ct reinfection and comparison between the treated (intervention) and untreated (control) groupsAmong participants in the control group, exploratory logistic regression to assess whether 50 immunogenetic biomarkers can predict Ct persistence and occurrence of PID

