Ethically, the deferred Ct analysis of collected vaginal samples until month 18 in the control group represented a challenge. However, the aim of the i-Predict trial is testing a systematic screening strategy and comparing it with the current strategy in France, which is to propose Ct testing in women younger than 25 years old in STI clinics, family planning and on specific indications by the general practitioner or gynaecologist. Therefore, all participants are given information on current guidelines for Ct screening. They are also given detailed information on chlamydia and the potential long-term complications of the infection, and they are encouraged to follow current guidelines for Ct screening and get tested whenever they wish [9]. Finally, all participants will benefit from a full gynaecological examination at the final visit and from treatment if necessary. Because participants in the control group are given information, they are more aware of the issues related to Ct infection and screening than the general population. This additional information might result in less statistical power to demonstrate the efficacy of systematic screening, but it was ethically unquestionable. The choice of the comparator group was discussed and maintained because it allows answering key questions on the natural course of Ct infection in the absence of any treatment. This trial will be the first large-scale test in Europe allowing determination of whether screening and treating young women decreases the risk of PID as well as documentation of key characteristics of Ct natural history (Additional file 1).

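### Spontaneous Ct resolution in controls is defined by swab results alone, so infections cleared by antibiotics outside the trial count as natural clearance

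*Protocol article*

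**What the plan says.** All statements are from the protocol article.

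- **Definition.** Secondary endpoints lists the "proportion of spontaneous Ct infection resolution (control group), defined as a Ct-negative sample after one or more Ct-positive" samples.
- **Analysis.** For controls with incident infection, Statistical analyses plans "proportions (and 95% CIs) of Ct infections with spontaneous resolution and of Ct infections evolving towards PID", together with "estimation of the duration of Ct infection (from Ct detection to clearance"). The same list labels the control group as untreated when reinfection is compared between arms.
- **Care open to controls.** Control group states: "During the whole study, participants will follow current screening guidelines (i.e., screening in case of symptoms or if they attend STI clinics"). Practical or operational issues adds that "they are encouraged to follow current guidelines for Ct screening and get tested whenever they wish". Under Follow-up, any participant who reports pelvic pain is contacted and encouraged to attend a gynaecology emergency department, and unscheduled visits to other physicians are expected.
- **Data on treatment.** The 6-monthly questionnaire asks about "additional testing since their previous sample, medical visits and antibiotic use (for Ct or other infections"). Forms completed by physicians record treatments given.
- **Purpose.** Control group explains deferred testing as a way to study the "natural course of Ct infection in the absence of testing and treatment". Practical or operational issues says the comparator was kept because "it allows answering key questions on the natural course of Ct infection in the absence of any treatment".

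**The concern.** The endpoint is called spontaneous, but the rule that decides it looks only at the order of swab results. A control who tests positive elsewhere, is treated and returns a negative swab at the next due date meets the definition exactly as an untreated woman who cleared the infection herself. So does a control who happens to take a Ct-active antibiotic for another infection. Duration from detection to clearance inherits the problem, because the end of the infection is the same negative swab.

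The error runs in one direction: clearance looks more frequent and infection shorter than they would be without treatment. It is likely to be greatest in women with symptoms, who have most reason to seek care. At stake is the quantity that the article gives as the reason for keeping a control arm with deferred testing.

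**Working it through.** The article states no figure for spontaneous resolution, so there is nothing to reproduce. The check is how far the recorded proportion departs from the intended one.

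**Inputs**
- s, true clearance between two swabs 6 months apart without treatment: not given. Gaps in knowledge says only that untreated infection may last a year or more. I assume a mean duration D of 1 to 2 years and a constant clearance rate, so s = 1 − exp(−0.5/D).
- t, share of control infections treated between the two swabs: not given. I take 5% and 20% purely as illustrations.
- Treatment always clears the infection, as Sample size assumes. Treatment is taken as independent of natural clearance, and reinfection before the next swab is ignored.

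**Step 1. True clearance**
- D = 1: s = 1 − exp(−0.5) = 39.3%
- D = 2: s = 1 − exp(−0.25) = 22.1%

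**Step 2. Recorded clearance = s + (1 − s)t**

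| D | True s | Recorded, t = 5% | Recorded, t = 20% |
|---|---|---|---|
| 1 year | 39.3% | 42.4% (+3.0 points) | 51.5% (+12.1 points) |
| 2 years | 22.1% | 26.0% (+3.9 points) | 37.7% (+15.6 points) |

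For example, at D = 2 and t = 20%: 0.221 + 0.779 × 0.20 = 0.377. With s = 0, which is the planning assumption in Sample size, the recorded figure would simply equal t.

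**Step 3. Duration implied by the recorded figure, −0.5/ln(1 − recorded)**
- t = 5%: 1.0 year reads as about 0.91, and 2.0 years as about 1.66.
- t = 20%: 1.0 year reads as about 0.69, and 2.0 years as about 1.06.

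This step depends on the constant-rate model, which is mine. Secondary endpoints records duration only in coarse 6-monthly classes.

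**Step 4. Scale against sampling error**
- Evaluable controls after 10% attrition: 2000 × 0.9 = 1800.
- Incident infections found at month 6 or 12, the only ones with a later swab, at 5% yearly incidence and 5% baseline prevalence: 1800 × 0.95 × 0.025 × 2 = 85.5. At 7% prevalence: 1800 × 0.93 × 0.025 × 2 = 83.7.
- 95% half-width with 85 infections: 1.96 × √(0.393 × 0.607/85) ≈ 10 points at s = 39%, and 1.96 × √(0.221 × 0.779/85) ≈ 9 points at s = 22%.

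A 5% treated share shifts the estimate by less than its sampling error. A 20% share shifts it by more.

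**The case against.** **The word itself restricts the endpoint.** One can argue that spontaneous already excludes treated women, that the clause after it only describes the swab evidence, and that antibiotic use is collected for this very purpose. The intent is indeed clear. But the article goes on to define the term, and that definition does not carry the intent out. The algorithm in Secondary endpoints that uses treatment information does not fill the gap: it separates reinfection, treatment failure and persistence, and does not reclassify a negative swab.

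**Censoring rules belong in the analysis plan.** This stands in part. The absence of a detailed censoring rule in a journal article would be no fault in itself. The fault is a stated definition that, if followed, gives the wrong quantity.

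**The effect may be small.** This also stands. No treated share is given, and at 5% the shift lies within sampling error.

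A reader might infer more than the text supports:
- *That the immunogenetic analysis is contaminated.* Its persistence outcome is not defined in the article as the complement of this resolution endpoint. The only rule given for persistent infection is the algorithm, which does use treatment.
- *That women with PID are counted both as progressing and as spontaneously resolved.* The definition allows this, but no section states that PID in controls is treated with antibiotics before the next swab. It is an inference from the treatments recorded on the forms and the planning assumption on treatment efficacy. The two proportions are also not presented as mutually exclusive.
- *That the treated share can be read off the article.* The 10% and 12% PID incidences among Ct-positive women in Sample size carry no stated period, so they give no yearly treatment rate. Nor does the roughly 70–80% asymptomatic share in Background show that the remaining 20–30% seek care and are treated between two swabs.

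**Conclusion.** The concern holds for the resolution endpoint and for duration from detection to clearance. As written, both count treated clearance as natural clearance, in an arm whose members are free to be tested and treated. The direction of the bias is certain if any control is treated successfully between swabs and would otherwise have remained positive. Its size is unknown: about 3 to 4 points at an assumed 5% treated share and about 12 to 16 points at an assumed 20%, for true 6-month clearance of 39% to 22%. These figures illustrate and do not predict.

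This should be fixed, but it is not critical. It concerns secondary natural-history endpoints. The primary comparison of PID incidence and the sample size do not depend on it. Treatment decided at the final visit adds nothing to the bias, because that visit follows the last scheduled swab.

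**What to change.** Redefine spontaneous resolution as a Ct-negative swab after a Ct-positive swab with no Ct-active antibiotic reported in between, whether it was given for Ct, PID or another infection. Take the information from the follow-up questionnaires and the physician and emergency department forms. In the resolution and duration analyses, censor the infection at the first such treatment or handle treatment as a competing event, and report treated clearance as its own category. Apply the same rule to the persistence outcome of the immunogenetic analysis if that outcome is derived from the same swab definition. Settle the wording before the deferred control swabs are analysed.

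The cost is a change to one definition and its analysis, with no new data collection. Fewer infections, out of roughly 85 expected, will inform natural clearance, so intervals will widen. Censoring also assumes that treated infections would otherwise have cleared at the same rate as untreated ones, which is doubtful if symptoms prompt treatment; presenting treatment as a competing event alongside it makes this visible. Antibiotic use is partly self-reported, so some treated clearances will still be missed.
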